# One-step partial or complete caries removal and bonding with antibacterial or traditional self-etch adhesives: study protocol for a randomized controlled trial

**DOI:** 10.1186/s13063-016-1484-0

**Published:** 2016-08-15

**Keywords:** Deep carious lesion, Cavity preparation, Partial caries removal, Permanent dentition, Dental adhesives, Composite resins, Pulp capping, Randomized controlled trial

## Abstract

**Background:**

Current concepts in conservative dentistry advocate minimally invasive dentistry and pulp vitality preservation. Moreover, complete removal of carious dentin in deep carious lesions often leads to pulp exposure and root canal treatment, despite the absence of irreversible pulp inflammation. For years, partial caries removal has been performed on primary teeth, but little evidence supports its effectiveness for permanent teeth. Furthermore, the recent development of new antibacterial adhesive systems could be interesting in the treatment of such lesions. The objectives of this study are to compare the effectiveness of partial versus complete carious dentin removal in deep lesions (primary objective) and the use of an antibacterial versus a traditional two-step self-etch adhesive system (main secondary objective).

**Methods/Design:**

The DEep CAries Treatment (DECAT) study protocol is a multicenter, randomized, controlled superiority trial comparing partial versus complete caries removal followed by adhesive restoration. The minimum sample size required is 464 patients. Two successive randomizations will be performed (allocation ratio 1:1): the first for the type of excavation (partial versus complete) and the second (if no root canal treatment is required) for the type of adhesive (antibacterial versus traditional). For the two objectives, the outcome is the success of the treatment after 1 year, measured according to a composite outcome of five FDI criteria: material fracture and retention, marginal adaptation, radiographic examination (including apical pathologies), postoperative sensitivity and tooth vitality, and carious lesion recurrence.

**Discussion:**

The study will investigate the interest of a conservative approach for the management of deep carious lesions in terms of dentin excavation and bioactive adhesive systems. The results may help practitioners achieve the most efficient restorative procedure to maintain pulp vitality and increase the restoration longevity.

**Trial registration:**

ClinicalTrials.gov Identifier NCT02286388. Registered in November 2014.

**Electronic supplementary material:**

The online version of this article (doi:10.1186/s13063-016-1484-0) contains supplementary material, which is available to authorized users.

## Background

Currently, caries management should be based on minimal intervention dentistry concepts [1], including minimally invasive cavity preparations when surgical intervention is required. However, with deep carious lesions, the most commonly used procedure is complete excavation in one step, with hardness to a dental probe used to assess caries excavation [2, 3]. This practice leads to a high risk of pulp exposure and poor prognosis in terms of maintaining pulp vitality [4].

Two alternative options have been proposed to minimize the risks of pulp exposure and postoperative pulpal complications.

The first strategy, chronologically, is the stepwise technique (complete excavation in two steps), with residual carious dentin at the pulpal wall of the prepared cavity left under a temporary restoration placed at the first visit followed by a complete excavation at a second visit (generally 2–6 months later). Clinical surveys have compared the stepwise technique with one-step complete excavation in permanent teeth [5, 6], primary teeth [7], and mixed dentition [8]. Nevertheless, the stepwise technique is time-consuming and costly, and pulp exposure occurs in 15–20 % of cases during the second excavation step [9].

The second approach, more controversial due to a paradigm shift, is partial (incomplete/selective) excavation. The clinical procedure is the same as with the stepwise excavation but without any second procedure. To avoid pulp exposure, carious dentin remains close to the pulp and the cavity is sealed with a definitive restoration. This concept is based on substantial evidence that removal of all carious dentin in deep carious lesions is not required for successful lesion management, provided that the restoration can effectively seal the lesion from the oral environment [10]. Studies have compared stepwise with partial excavation techniques only in permanent teeth [11, 12] or complete excavation in one step with partial excavation essentially in primary teeth [13–17] and mixed dentition [8]. Partial excavation results in lower long-term costs, longer-retained teeth and better pulp preservation than complete excavation (in one or two steps). However, because of high risk of bias within studies, more randomized clinical trials are needed for definitive conclusions [9, 18, 19].

Two multicenter randomized clinical trials are currently ongoing, one comparing selective and stepwise excavation of deep carious lesions in primary molars [20] and our study comparing complete excavation in one step to partial excavation in permanent teeth.

Furthermore, after dentine excavation, different materials may be used to restore the loss of tooth substance [21]. Glass ionomer cements (GIC) are commonly used because of their biocompatibility, fluoride release and adhesive properties, but they have weak mechanical and aesthetic properties [22]. Dental composite resins have high mechanical and good aesthetic properties but limited bioactive properties [23] and require a specific adhesive system. Few clinical studies have evaluated the role of antimicrobial agents incorporated into restorative materials and their potential anti-caries effect [24]. An effective bactericidal effect from adhesive systems could be an alternative to suppress residual contamination after caries removal [25], even more so with incomplete eviction. Adhesive systems usually have limited bioactivity. A new adhesive, Clearfil™ SE Protect (Kuraray Europe Gmbh, Hattersheim, Germany), is the only adhesive system considered to have antibacterial properties. This adhesive system contains 12-methacryloyloxydodecylpyridinium bromide (MDPB), which inhibits the proliferation of bacteria involved in dentinal caries like *Streptococcus mutans*, *Lactobacillus casei* and *Actinomyces naeslundii* and reduces lactic acid production of *S. mutans* [26–30]. Moreover, it has been shown that, in vivo, this adhesive system can induce the inhibition of caries progression [31] and preservation of pulp vitality [32].

However, no clinical study has evaluated this type of adhesive for conservative treatment of deep carious lesions.

### Objectives and hypotheses

The aim of this clinical trial is to support a management strategy that preserves pulp vitality in cases of deep carious lesions with partial caries removal, followed by a composite restoration, in a single session.

The primary objective is the comparison of the efficacy (binary success criteria) of partial (P) versus complete (C) excavation in deep carious lesions of mature permanent teeth at 1 year. The main secondary objective is the efficacy (binary success criteria) of an antibacterial adhesive (AA) versus a traditional two-step self-etch adhesive (TA) at 1 year. Two secondary objectives will be also considered: (i) the identification of predictive factors for success at 1, 2, and 3 years and (ii) the description of the consequences of treatment failure and side effects for each treatment arm.

The underlying pathophysiological hypotheses are that (1) partial excavation would imply less irreversible pulp diseases as compared with complete excavation in one step and (2) the antibacterial adhesive system would help prevent secondary caries.

## Methods/design

### Trial design

The Standard Protocol Items: Recommendations for Interventional Trials (SPIRIT) guidelines [33] have strictly been followed in the planning of this trial (Additional file 1).

This trial is a multicenter intention-to-treat randomized controlled superiority trial with parallel arms. Analysis of results will be performed according to the intention-to-treat principle. For the primary objective, only patients are blinded to the allocated intervention (partial or complete caries removal). For the secondary objective (type of adhesive), both patients and investigators are blinded. Outcome examiners and data analysts are always blinded.

Two successive randomizations are performed (allocation ratio 1:1): first, for the type of excavation (P versus C) and second, for the adhesive system (AA) versus TA. The second randomization is not performed for teeth requiring endodontic treatment after the first randomization.

The possible combinations of interventions are in Fig. 1, the flow diagram is mentioned on Table 1 and the flow chart of the study is in Fig. 2.

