### Implementation

The minimization algorithm was implemented by statisticians and methodologists independently of investigators. Patients are assigned to interventions arm by the investigators.

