### Intervention

At the first visit, eligibility criteria are verified by an investigator. Information about the study is then given to the patient and the inclusion is formalized by the signing of the informed consent form.

A clinical examination is performed, then (1) pulp vitality is assessed with thermal (cold) and electrical methods (Elements Diagnostic Unit and Apex Locator®, Kerr Endodontique, Bioggio, Switzerland); and (2) bite-wing and retroalveolar radiographs are taken by using film-holders supplied by Kerr Endodontique. Bite-wing radiographs allow for assessing the depth of the lesion: no continuity between the carious lesion and the pulp chamber should be seen; and retroalveolar radiographs allow for determining the periapical index [46]. In case of multiple carious lesions, the lesion that best meets the inclusion criteria and allows for the best handling (easy access) is chosen. Other lesions will be further treated according to usual procedures and will not be entered in the study.

At the second visit, an investigator performs the tooth restoration. The tooth is anesthetized. The shade of the tooth-colored restoration is selected before isolation with the rubber dam. The first randomization is achieved. The superficial necrotic tissues and peripheral demineralized dentin are removed with complete excavation to avoid excavation close to the pulp. The bulk of the carious dentin is removed by using sterile round ceramic burs (Komet France, Paris, France) under water spray cooling and the final excavation with hand instruments. The excavation is controlled by use of an intraoral light-induced fluorescence camera (Soprolife®, Acteon Group, La Ciotat, France) and the corresponding image is registered. According to the manufacturer of the Soprolife® camera, infected carious tissues appear green-black in fluorescence. The infected/affected dentin interface emits bright red fluorescence in active lesions and dark red fluorescence in arrested lesions. The underlying dentin looks gray-green in fluorescence [47].

For cases under P excavation, the investigator stops excavating when the dentin close to the pulp appears bright or dark red after removal of the green-black infected dentin.

For cases under C excavation, the investigator stops excavating when the dentin close to the pulp appears gray-green after removal of the green-black infected dentin and removal of the bright or dark red infected/affected dentin interface.

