With pulp exposure < 2 mm^2^ after C excavation, the exposed pulp is irrigated with chlorhexidine. Following hemostasis (within 5 minutes), a tricalcium silicate cement (Biodentine™, Septodont, Saint Maur des Fossées, France) is applied according to the manufacturer’s instructions. After complete cement setting (within 15 minutes), the cavity is restored following the same clinical procedures as for cases without pulp exposure.

With pulp exposure > 2 mm^2^ and/or no hemostasis, a root canal treatment is performed, and the case is considered a failure for randomization 1 but not randomization 2.

Cases undergo randomization 2 to determine the adhesive system: Clearfil™ SE Bond (Kuraray Europe) or Clearfil™ SE Protect (Kuraray Europe) (i.e., TA and AA, respectively). Enamel and dentin are prepared according to the manufacturer’s instructions. The tooth is restored by using the Gradia® Direct Flo and Gradia® Direct Posterior composite resin (GC Europe N.V., Leuven, Belgium) in accordance with the manufacturer’s instructions and if necessary a matrix system (Kerr Restauration, Bioggio, Switzerland). The photo-polymerization steps involve use of a LED curing light (Demi™ Ultra, Kerr Restauration, Bioggio, Switzerland). Then, a bite-wing radiograph is taken as a control.

Various strategies are implemented to improve adherence to intervention protocols: the investigator must submit the fluorescence image obtained after caries removal as well as the control radiograph to the randomization website. He must also indicate the adhesive applied.

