All current recommendations (the SPIRIT statement) were taken into account for the design of the present clinical trial [33]. A complete factorial design would have allowed for exploring the interaction between the management strategies (P versus C excavation, and AA versus TA). However, the impossibility of randomizing the adhesive with endodontic treatment, expected to be more frequent with C excavation, led us to adopt a nested design with two distinct and successive randomizations. The tooth was chosen as the statistical unit, with only one tooth per patient, to ensure the independence between statistical units. If a split-mouth design had been chosen, finding patients with two cavities similar in depth would have been difficult. In terms of internal validity, the sources of bias are limited by the use of centralized randomization (selection bias), strict prospective data record and monitoring (information bias), and blinded patients and evaluators (performance and detection bias). However, because of the nature of the investigation, the investigators cannot be blinded.

The choice of assessment criteria is based on the 16 criteria for evaluating direct restorations published and approved by the FDI [48]. As suggested by Hickel et al., a selection of criteria was chosen to match the objectives of the study [49]. The focus was functional properties (material fracture and retention, marginal adaptation, radiographic examination) and biological properties (postoperative pain and tooth vitality, recurrence of carious lesions).

The clinical procedure is carried out under optimal conditions. One of the main points is that partial removal involves only the tissues close to the dental pulp. Indeed, the cavity margins should include no carious tissue so as to avoid the recurrence of the lesion at the tooth-restoration interface. Decay can reach different surfaces of the tooth, but the restoration must be single and unique to avoid any confusion during the evaluation step. For the same reason, the included tooth must be free of cervical carious lesion.

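### The protocol contradicts itself on whether the operating investigator is blinded to the adhesive, and investigator scores can enter that comparison

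*Protocol article*

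**What the plan says.** Trial design (Methods/design) treats the two comparisons separately. For excavation, only patients are blinded. For the adhesive: "For the secondary objective (type of adhesive), both patients and investigators are blinded". It adds: "Outcome examiners and data analysts are always blinded".

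Intervention describes who does what. "At the second visit, an investigator performs the tooth restoration". The second randomization selects one of two products given by trade name, Clearfil SE Bond (TA) or Clearfil SE Protect (AA). To support adherence, the investigator uploads the fluorescence image and the control radiograph to the randomization website, and the text continues: "He must also indicate the adhesive applied". Implementation says: "Patients are assigned to interventions arm by the investigators".

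The Discussion, in its paragraph on design and internal validity, credits the blinding of patients and evaluators with limiting performance and detection bias. It then concedes that "because of the nature of the investigation, the investigators cannot be blinded".

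Two further provisions bear on the outcome. Outcome measures assigns scheduled FDI scoring at 1, 2 and 3 years to two blinded independent evaluators, but gives emergency-visit scoring to the investigator. Statistical methods uses the last assessment by the investigator, where one exists, for patients who do not attend follow-up, and applies similar analyses to AA versus TA.

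**The concern.** A person who reports which adhesive was applied would ordinarily know which adhesive was applied. Read plainly, the reporting duty and the Discussion sentence both run against the claim in Trial design, and they concern the same people.

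This is more than a stylistic slip, for two reasons. Blinding of the operator is a stated property of the main secondary comparison, and a trial report would normally repeat it. The investigator can also supply outcome data. If investigators know the adhesive, that knowledge could influence how the restoration is placed and how the FDI criteria are scored at an emergency visit. Where the patient then misses the scheduled visit, that score may be the one analysed.

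**Working it through.** No figure in the plan is at stake, so the check sets the statements side by side.

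| Section | Who | Statement on the adhesive |
|---|---|---|
| Trial design | Investigators | Blinded |
| Intervention | Investigator placing the restoration | Reports the adhesive used |
| Discussion | Investigators | Cannot be blinded; no comparison named |
| Trial design | Patients, outcome examiners, analysts | Blinded |
| Outcome measures | Two scheduled evaluators | Blinded, independent |
| Outcome measures | Investigator, emergency visits | Scores the FDI criteria; blinding not mentioned |

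**Step 1: is it the same role?** Yes. Intervention has an investigator perform the restoration, and the reporting duty falls on that investigator. Trial design and Discussion use the same word.

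**Step 2: can the statements be made consistent?** Two conditions are needed together. The adhesive reported would have to be a neutral code and not a product, and the Discussion sentence would have to refer to excavation only. The article states neither. It also does not rule either out.

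**Step 3: does an investigator's score reach the analysis?** Emergency visits are the only post-treatment assessments that the article gives to the investigator to score. The missed-visit rule in Statistical methods then carries the last investigator assessment into the analysis. Together these form a route from an investigator's score to the AA-versus-TA outcome. For a tooth on that route, the examiner is an investigator, so "Outcome examiners and data analysts are always blinded" is only as secure as the disputed claim.

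**Step 4: how many teeth could take that route?** The article does not say. For scale only, Sample size plans for at most 10 % lost to follow-up at 1 year, with a minimum of 464 patients. Assume that this ceiling also describes the share missing the 1-year visit. Then 0.10 × 464 = 46.4, or about 46 patients at the minimum sample size. The affected teeth would be fewer, because only patients with an investigator assessment count, and teeth needing root canal treatment never reach the second randomization. This counts teeth that might be exposed; it does not estimate bias.

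**The case against.** The strongest reply is that the article is a condensed account and the statements may all be true. Reporting the adhesive could mean entering a bottle or kit code. Trade names tell the reader what is compared, not how the operator's bottles are labelled. The Discussion describes the reference adhesive as similar to the test product apart from the antibacterial component, so masking is plausible, and labelling detail belongs in the full protocol. The Discussion sentence on investigators may have only the excavation comparison in mind, where Trial design already concedes that investigators know the arm.

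Much of this stands. A reader might infer that the operator is in fact unblinded and that AA versus TA lacks its stated blinding. The article does not establish that. Nor does it say that the investigator who scores an emergency visit is the one who placed the restoration.

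What does not stand is that nothing needs correcting. The point does not rest on a missing description of masking. It rests on statements that conflict as worded. Reading the Discussion sentence as limited to excavation would still leave Trial design and Intervention at odds.

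**Conclusion.** The article is inconsistent on whether the operating investigator is blinded to the adhesive, and Trial design, Intervention and Discussion must be reconciled. The doubt is confined to the investigator and to outcomes the investigator scores. Blinding of patients, scheduled evaluators and analysts is untouched by anything in the text.

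The size of any bias cannot be computed. A reader might try to gauge it from the planned success rates of 97 % and 90 %, which average to a failure rate of (3 % + 10 %)/2 = 6.5 %, and conclude that a few investigator-scored teeth could decide the result. The article does not support that. The 6.5 % is an average over the excavation arms, and root canal treatment after a large exposure counts as failure for the first randomization but not the second. No failure rate is given for AA or TA. Nor is 464 an upper limit on the teeth affected; it is the minimum enrolment.

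The conclusion rests on reading the reporting duty and the Discussion sentence as printed. It would reduce to a wording correction if the full protocol shows a coded supply. It matters for the main secondary objective and does not alter the sample size, power or alpha.

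**What to change.** Establish which situation applies, then make the text agree.

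- **If the adhesives are supplied under a neutral code:** say in Intervention that the investigator reports the code, and limit the Discussion sentence to the excavation comparison.
- **If they are not:** delete investigator blinding from Trial design. Describe AA versus TA as blinded to patients, scheduled evaluators and analysts only, and qualify the statement about outcome examiners for investigator-scored cases. Add a sensitivity analysis of AA versus TA that sets aside all investigator-scored outcomes and treats those teeth as missing.

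The exclusion must cover successes and failures alike. Removing only investigator-scored successes would make exclusion depend on the outcome and would keep the failure scores that are equally open to question.

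The first option costs two clarifying phrases. The second costs a slightly weaker stated blinding and one extra analysis on somewhat fewer teeth. Under Ethical consideration, any protocol amendment also goes to the scientific board, the ethics committee and the national agency. Changing the supply at this stage would probably help few patients: inclusion was planned to end in July 2016 and the article appeared in August 2016, although it still describes the trial as recruiting.

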### Outcome measures

Cases are considered successful if each of the following five FDI World Dental Federation (FDI) criteria has a final score ≤ 3: material fracture and retention, marginal adaptation, radiographic examination (including apical pathologies), postoperative sensitivity and tooth vitality, and recurrence of carious lesions [48, 49]. A score of 4 or 5 indicates that reintervention is necessary and, therefore, the case is classified as a failure in the context of the study. Criteria are scored at 1, 2, and 3 years’ postintervention by two blinded independent trained evaluators. Study assessing the agreement between evaluators for FDI criteria is ongoing. In cases of emergency visits, FDI criteria will be scored by the investigator.

For the primary objective (P versus C excavation) and the main secondary objective (AA versus TA), the outcome will be the success (yes/no) at 1 year, as defined previously.

For the first secondary objective (identification of factors predicting success at 1 and 3 years), the following candidate factors will be investigated: postoperative pain, patient age, type of carious lesion (primary or secondary), location of the carious lesion, and pulp exposure.

For the second secondary objective (description of the consequences of treatment failure and side effects per treatment arm), the following events will be considered: total number of needed visits, number of endodontic treatments, and number of avulsions.

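### The statement that outcome examiners are always blinded holds only for scheduled visits; for partial versus complete excavation, some primary outcomes are set by an investigator who knows the arm

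*Protocol article*

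**What the plan says.** Trial design gives three statements on blinding. For excavation: "For the primary objective, only patients are blinded to the allocated intervention (partial or complete caries removal". For the adhesive: "For the secondary objective (type of adhesive), both patients and investigators are blinded". And without restriction: "Outcome examiners and data analysts are always blinded". The Discussion counts "blinded patients and evaluators (performance and detection bias") among the features that limit bias, then adds: "However, because of the nature of the investigation, the investigators cannot be blinded".

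Outcome measures assigns the 1-, 2- and 3-year scoring of the five FDI criteria to two blinded, independent, trained evaluators. The same article gives three other ways in which a primary outcome is set:

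- **Restoration visit (T0).** Under Intervention, "At the second visit, an investigator performs the tooth restoration". If the stated exposure or hemostasis condition is met, "a root canal treatment is performed, and the case is considered a failure for randomization 1".
- **Emergency visits.** Outcome measures: "In cases of emergency visits, FDI criteria will be scored by the investigator". Table 1 allows these visits at any time between T0 and 3 years.
- **Missed follow-up.** Statistical methods says that when a patient does not attend, the investigator's most recent assessment, if one exists, is used in the analysis.

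Nothing in the article says that blinded evaluators review or re-score any of these cases.

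**The concern.** The article offers blinded assessment as its protection against detection bias in a trial whose operators cannot be blinded. On three routes the person who sets the primary outcome is such an operator, or at least an investigator who is not blinded to excavation.

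These routes are likely to matter for the primary comparison. The first hypothesis under Objectives is that partial excavation leads to less irreversible pulp disease, and the Discussion expects endodontic treatment to be more frequent after complete excavation. Pulpal events of this kind can plausibly arise at T0 or bring a patient in as an emergency, which is where blinding is absent. Knowledge of the arm could move these calls in either direction.

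A reader who takes the blinding statement at face value would therefore credit the primary result with more protection than the design gives it.

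**Working it through.** **1. Who sets the outcome, and is that person blinded to P or C?**

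| Route | Who decides | Blinded to excavation? | Section |
|---|---|---|---|
| Root canal treatment at T0 | Investigator | No | Intervention; Trial design |
| Emergency visit, FDI score | Investigator | No | Outcome measures; Trial design |
| Missed visit, last assessment used | Investigator | No | Statistical methods; Trial design |
| Scheduled visit, FDI score | Two evaluators | Yes | Outcome measures |

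The unqualified statement is met only in the last row.

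**2. Reproducing the sample size.** Inputs from Sample size and Statistical methods: success 97 % (P) and 90 % (C), two-sided alpha 5 %, power above 80 %, 10 % loss, Fisher's exact test; allocation 1:1 from Trial design. Exact enumeration of Fisher's test gives power of 79.9 % with 208 per arm and 80.1 % with 209. Then 2 × 209 = 418, and 418 / 0.9 = 464.4, against 464 stated. The figure reproduces and this point does not affect it.

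**3. Expected failures.** With 209 analysed per arm, P: 0.03 × 209 = 6.3; C: 0.10 × 209 = 20.9. That is about 6 and 21, or 27 in all. With all 232 per arm, 6.96 and 23.2, about 7 and 23.

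**4. How many calls change the result?** Two-sided Fisher p, failures in P v C:

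| Per arm | P v C | p |
|---|---|---|
| 209 | 6 v 21 | 0.0045 |
| 209 | 6 v 16 | 0.046 |
| 209 | 6 v 15 | 0.071 |
| 209 | 9 v 21 | 0.036 |
| 209 | 10 v 21 | 0.060 |
| 232 | 7 v 23 | 0.0039 |
| 232 | 11 v 23 | 0.049 |
| 232 | 12 v 23 | 0.078 |

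Starting from the expected counts at 209 per arm, six fewer C failures or four more P failures take p above 0.05. At 232 per arm, four more P failures do not (0.049) and five do (0.078).

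**5. Illustration under no true difference.** Assumptions, none of them from the article: 209 per arm, equal true success, a share s of C teeth scored by the investigator, and an added failure probability q for those teeth. Observed C success is then the true success minus s × q. At true success 93.5 %, the Fisher rejection rate is 3.1 % with no bias, 4.6 % at s = 10 %, q = 0.1 (shift 0.01), 8.7 % at q = 0.2 (shift 0.02) and 15.7 % at q = 0.3 (shift 0.03). For s = 10 % and q = 0.2, over true success from 90 % to 97 %, the range is 7.6 % to 12.0 %. The article gives neither s nor q, so these figures show sensitivity and are not an estimate of bias.

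**The case against.** The strongest reply is that there is no literal contradiction. Data collection methods distinguishes investigators from evaluators, whom it also calls examiners. On that reading the examiners are the two evaluators, nothing says they are unblinded, and the article openly discloses that investigators are not blinded to excavation. This stands as a reading of one sentence. It does not rescue the detection-bias claim, because the article itself has non-examiners set some primary outcomes.

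The T0 decision has a written rule, must be made during treatment and cannot be blinded. This also stands: it is an inherent and disclosed limit, to be made visible in the report rather than removed.

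An emergency score is not automatically the 1-year outcome, since a patient seen in an emergency may still attend the scheduled visit. That is correct. What makes the route real is the rule in Statistical methods that brings the investigator's last assessment into the analysis when visits are missed.

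A reader might go further and infer that 1-year radiographs reveal the arm, or that dentin left in arm P would be read as recurrence, so that blinding fails at scheduled visits too. The article does not say this. Its remark on bite-wings and lesion depth concerns the examination before treatment, and recurrence is listed as a criterion separate from radiographic examination. The evaluators are trained and work to consensus. Both possibilities are at most risks to note. Comparing with the control film taken at T0 would not be a safe answer, because by the same reasoning that film could reveal the arm.

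**Conclusion.** The point holds for the P versus C comparison. The blinding statement in Trial design and the reliance on it in the Discussion are accurate for scheduled visits only. They do not cover T0 root canal failures, emergency scores, or investigator assessments carried into the analysis.

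With about 27 failures expected under the planning rates, around four to six reclassified teeth would be enough to change significance at 209 per arm. That depends on the planned success rates being right. How many outcomes will actually come from an unblinded investigator is not stated, and no particular share should be assumed.

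A reader might infer that protection against detection bias is absent altogether. The documents do not support that: two blinded evaluators score the scheduled visits, and nothing in the text contradicts their blinding. Nor does the point extend to the adhesive comparison. Trial design says investigators are blinded there, and cases needing endodontic treatment at T0 do not enter the second randomization. The Discussion's unrestricted remark that investigators cannot be blinded should simply be limited to excavation.

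**What to change.** 1. Limit the blinding statements in Trial design and Discussion to scheduled visits, and reconcile them with Intervention, Outcome measures and Statistical methods, so that each route to a primary outcome names who decides and whether that person knows the excavation arm.
2. Where an emergency or carried-forward investigator score enters the 1-year outcome, have the existing blinded evaluators re-score, from records with the arm masked, those criteria that the records allow. Keep the investigator's score as supportive.
3. Report primary failures by source (T0; emergency or carried-forward; scheduled blinded visit) and by arm. Add a sensitivity analysis that does not rely on investigator-scored FDI outcomes. One simple form treats those scores as missing and applies the three missing-data scenarios already planned, with T0 root canal cases kept as failures. Simply excluding these patients would be weaker, since an emergency visit is itself related to outcome.

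The cost is a little evaluator and analysis time, some work to mask records, and changes of wording. No treatment procedure and no sample size changes. The remedy is partial: sensitivity and vitality, and marginal adaptation, cannot be fully re-scored from records, and the T0 decision stays unblinded.
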